# Can home care work be organized to promote musculoskeletal health for workers? Study protocol for the Norwegian GoldiCare cluster randomized controlled trial

**DOI:** 10.1186/s12913-022-08916-0

**Published:** 2022-12-07

**Keywords:** Goldilocks work principle, Workplace health promotion, Occupational health, Musculoskeletal pain, Lower back pain, Neck pain, Shoulder pain, Cluster-randomized controlled trial

## Abstract

**Background:**

Home care workers perform physically strenuous tasks, in particular when handling patients with high care demands. Thus, musculoskeletal pain and sick leave is greater in this group than in the general population. To ease these issues, we will implement a Goldilocks Work intervention (GoldiCare), redistributing schedules between workers to achieve a “just right” weekly structure of physical work that can promote health. This protocol paper describes the content, design, implementation and evaluation of the cluster randomized controlled trial of the GoldiCare intervention in home care.

**Methods:**

The cluster randomized controlled trial is a 16-week workplace organizational intervention implemented through operations managers at the home care units. The operations managers will be introduced to the Goldilocks Work Principle and a GoldiCare tool, to assist the operations managers when composing a “just right” distribution of work schedules throughout the week. The GoldiCare tool provides an overview of the physical strain for each shift, based on the number of patients and their need for care. We expect to include 11 units, which will be randomized to either intervention or control at a 1:1 ratio. Home care workers assigned to the control group will continue to work as normal during the intervention period. Musculoskeletal pain in neck/shoulder and lower back will be the primary outcomes and we will also evaluate the composition of physical behaviors as well as fatigue after work as secondary outcomes. We will collect data using (1) daily questions regarding musculoskeletal pain and fatigue after work, (2) 7 days of objective measurements of physical behavior, (3) questionnaires about the participant’s characteristics, health, and workplace psychosocial stressors and (4) information on the implementation of the GoldiCare tool. In addition, a process evaluation will be conducted using focus group discussions and individual interviews.

**Discussion:**

Due to the increasing aging population in need of care, measures that can improve the health of home care workers are paramount for the sustainability of this sector. This organizational intervention is based on information available nation-wide, and therefore has the potential to be scaled to all municipalities in Norway if proven effective.

**Trial registration:**

This clinical trial was registered on 08/05/2022 under NCT05487027.

## Background

Home care workers care for patients living at home. The workers need to adapt to the patients’ health, functional abilities and living circumstances, such as crowded and small residences that are frequently insufficiently equipped for the required care tasks [1]. As a result, home care workers may spend considerable periods of time in awkward postures, often involving pulling and pushing while caring for patients [1, 2], and home care workers often find their work physically strenuous [3–5]. As a likely consequence, home care workers often report musculoskeletal pain and sick leave; as illustrated by their 11% sick leave rate, almost double the national average [6–8]. As the number of elderly aged above 65 is forecasted to double by 2050, and that of those aged above 80 years to triple [1, 9, 10], the home care workers are expected to play a crucial role in future health care service, as the home care sector offers a cost-effective solution for providing care [10–12]. However, to keep up with the increasing demands, the employees working in this sector must be healthy and working.

A way of improving employee health and limit sick leave might be to redesign work according to the Goldilocks Work Principle, which aims to make the physical work demands “just right.” [13, 14] A just right task distribution entails that workers are exposed to neither too little nor too much physical strain; both scenarios may lead to unfavorable exposures and thus suppress health [15]. Moreover, the vision of the Goldilocks Work Principle is that the just right distribution not only prevents poor health, but also promotes workers’ health and capacity. While the feasibility of Goldilocks interventions have been investigated in other sectors, such as child care [16] and manufacturing [17] no randomized controlled trial has been conducted in home care to date.

As a part of an earlier investigation, we noted a high prevalence of musculoskeletal pain in the neck/shoulder area (36%) and lower back (34%) among home care workers in Trondheim, Norway [2]. Further, we found long durations of awkward postures such as forward trunk inclination and arm elevation during the working day [2] which is documented to increase the risk of sick leave [18, 19]. In addition, the strenuous tasks were unevenly distributed among workers and a substantial proportion of employees were exposed to very high levels of physical strain [2], likely to lead to a substantial risk of musculoskeletal pain and sickness absence. Available evidence indicates that strenuous activities such as pulling, pushing, lifting, and leaning forward are frequently performed by home care workers caring for patients with extensive care needs [20, 21]. Patients who are admitted into the Norwegian home care system, are assessed by a trained nurse in terms of their care needs based on the International Classification of Functioning, Disability and Health system developed by WHO [22, 23], resulting in an activities of daily living (ADL) score. The total score is the average of five subcategories; 1) social function, 2) cognitive function, 3) ability to take care of their own health, 4) domestic responsibilities, and 5) self- care. Home care workers are mainly responsible for assisting with self-care and therefore we investigated if patients’ self-care ADL (hereafter referred to as “ADL”) score was associated with the physical work demands of home care workers. We found patients with a high ADL score (4–5, out of 5) to require the home care workers to stand for relatively longer durations, compared to when caring for low ADL patients (1–2, out of 5). Previous studies and our pilot investigations imply that ADL scores may potentially act as a proxy for the physical work demands put on the home care workers. Due to the handling of patients being a major source of exposure to physical work demands, the ADL scores may be used to redesign the uneven distribution of physical work demands into being “just right”, which could improve the musculoskeletal health of home care workers.

In this protocol paper, we describe a cluster randomized controlled trial developed to evaluate the effectiveness of a Goldilocks Work intervention in promoting musculoskeletal health among home care workers.

### Trial design

This Goldilocks work intervention will be implemented as a cluster randomized controlled trial with two parallel groups—a no-intervention control arm and an intervention arm, with clusters allocated to the control and the intervention groups in a 1:1 ratio.

## Methods—participants, interventions, and outcomes

### Study setting

The intervention will be conducted in Trondheim municipality, and an invitation for voluntary participation was distributed to all 13 home care units operating in this area. Eleven positive responses were received. Each home care unit in Trondheim municipality employs 23–95 home care workers providing health services to patients living in their private homes within a defined geographical area. Each unit is organized in teams, which are responsible for a smaller section of the unit, often demarcated by geography. This organizational structure ensures home care workers’ familiarity with the patients, thereby increasing effectiveness, efficiency, and work quality. Seeing familiar home care workers every day also gives structure and reassurance to the patients. The operations manager distributes the daily working lists defining the assignments of each home care worker and an approximate timeframe for the visit to each patient.

### Eligibility criteria

As the intervention is conducted at the organizational level, all employees working at a unit randomized to the intervention arm will be affected regardless of their participation in study-specific measurements. However, all home care workers with ≥50% employment will be invited to participate in baseline measurements unless they are pregnant, have a fever, are allergic to the tape used to attach the sensors, or have a physical impairment that precludes normal physical activity. Home care workers volunteering to participate will be required to read and sign an informed consent form before enrolment in the measurements, clearly explaining their rights in accordance with the Declaration of Helsinki.

### Intervention

#### Development

The intervention was developed in accordance with the intervention mapping strategy [24]. The first step involved formulating a “logic model of the problem” describing the population at risk and the context. Next, the “logic model of change” was developed, whereby the intervention outcomes and objectives were defined based on the findings obtained in the first step. In the last step, an intervention comprising both evidence- and theory-based methods was designed, securing that it will be appropriate for the given context and problem.

#### Logic model of the problem

To measure the physical behavior (e.g., sitting, standing, walking and running etc.) and its intensity during a typical workday, an observational study involving 6 units in Trondheim municipality was conducted using accelerometers and heart rate monitors [2]. Analysis of the data revealed a considerable variation between home care workers in the time spent in awkward postures, i.e. arm elevation and forward trunk inclination. Also, a high proportion of workers reported long-term (≥3 consecutive months in the past year) neck/shoulder pain (36%) and lower back pain (34%) [2].

#### Logic model of change, program outcomes and objectives

A participatory approach was adopted to identify potential areas of focus for the intervention, with eight home care workers and five operations managers taking part in digital workshops. They communicated that the patient visits were unevenly distributed among the home care workers, in terms of patients requiring extensive care and light care. We examined the patients’ ADL scores, assuming that they reflect the level of care for the patient, and thus can serve as a proxy for the physical work demands of the home care worker [20, 21]. To check this assumption, we used objective physical activity data from a feasibility study in home care and associated them with ADL scores of the patients visited during selected shifts. The results confirmed that workers caring for patients with a higher ADL score had, on average, a higher physical work load compared to when looking after patients with lower ADL scores (unpublished data).

Based on these findings, our intervention objective was to promote musculoskeletal health in the neck/shoulder area and in the lower back by ensuring that home care workers do not receive disproportionate numbers of patients with a high ADL score within a week, as shown in the program logic model in Fig. 1. A variation for the individual home care worker between working lists with many high ADL patients and working lists with few or no high ADL patients, offers an alternation between higher and lower strain. The choice to aim for a weekly just right distribution of physical strain instead of a daily just right distribution was a result of the working lists being designed and scheduled based on several factors that could not be controlled as a part of the intervention, such as geography, technical skills, qualifications, and time management. Thus, changing the working lists within a workday was not a feasible strategy.

**Fig. 1 Fig1:**
[figure not shown]
Program logic explaining the problem at hand, the intervention aims, and the expected outcome of the intervention. *ADL* Activities of Daily Living

#### Program design and production

The “GoldiCare” intervention described here was developed in accordance with the Goldilocks Work Principle, which aims at improving worker health by re-designing work at the organizational level without compromising productivity [13]. The intervention was also developed in cooperation with the municipality as a nurse from one of the participating home care units is a member of the research team, contributing with important knowledge and experience of conditions in home care.

As part of the intervention, each operations manager will be provided with a “GoldiCare tool” developed in Microsoft Excel to support a more even distribution of high ADL patients among home care workers. The GoldiCare tool was inspired by a similar Goldilocks Work intervention implemented in Denmark [17]. The GoldiCare tool was tested in a feasibility study (unpublished), and an adjusted version was adopted for the present intervention. When using the GoldiCare tool, the operations managers will work towards achieving an even distribution between low and high strain days as days with medium strain are regarded to be “just right”. Operations managers define the strain level for the working day, based on the number of patients with high ADL scores on the working list. Since the total number of high ADL patients differs between units, the average physical work demand, as expressed by the ADL scores, differed between units. The GoldiCare tool eventually results in a weekly summary for each employee based on the composition of high, medium and low strain days throughout the week, and serves to inform the operations managers of any major differences between home care workers in the allocation of high ADL patients. The weekly summary per employee is used to obtain an overall summary for the entire unit, reflecting how well the operations managers implemented the intervention at the unit. Thus, the GoldiCare tool serves several objectives: [1] operations managers can use it to review previous and planned shifts, and can thus better distribute physically strenuous work in line with the Goldilocks Work Principle to give a sustainable practice in the long term, [2] both researchers and operations managers can gain insight into the level of physical strain among home care workers in a working week, and [3] both researchers and operations managers can quantitatively assess home care unit’s compliance with the intervention.

#### Implementation plan

The intervention described above will be implemented in a two-step process. In the first step, lasting for a total of 3 weeks, operations managers will get a thorough and personalized introduction to the GoldiCare intervention, including its aims and underlying scientific basis, and the usage of the GoldiCare tool. During this introduction, the percentage of high ADL patients required to define a working list as ‘high strain’ will be determined by the operations manager and the researchers together. In the two subsequent weeks, the operations managers will use the GoldiCare tool in their planning, and the researchers will visit each unit to assist and give guidance if needed. The second step will run throughout the intervention period, allowing the operations managers to use the GoldiCare tool in practice and receive timely feedback from the researchers. The feedback will include how the unit’s performance of the week compared to previous weeks, and the summaries of individual home care workers. The operations managers will be encouraged to contact the researchers at any point during the intervention period if problems or questions arise. To allow researchers an overview of the usage, the GoldiCare tools will be saved and edited in a cloud-based server.

#### Outcomes

##### Primary outcomes

Difference between intervention and control group in the change from pre- to post-intervention of lower back pain intensity.Difference between intervention and control group in the change from pre- to post-intervention of shoulder/neck pain intensity.

Both primary outcomes will be measured after each working day during 1 week at baseline and 1 week at the end of the intervention, using a 11-point numeric scale (0–10).

##### Secondary outcomes

Difference between intervention and control group in the change from pre- to post-intervention of the composition of awkward postures (arm elevation and trunk inclination), assessed by accelerometers.Difference between intervention and control group in the change from pre- to post-intervention of the composition of physical behavior (standing, sitting and physical activity), assessed by accelerometers.Difference between intervention and control group in the change from pre- to post-intervention of fatigue, measured after each working day for 1 week using a 11-point numeric scale (0–10).Compliance with the intervention, as determined by the units’ weekly summary. For this purpose, the weekly summary of variables calculated in the GoldiCare tool will be compared to the baseline.

### Sample size

Preliminary mapping of the Trondheim home care sector indicated that 440 home care workers meet the ≥50% employment criteria. As our previous investigation of the home care sector [2] had a 58% participation rate, we expect that 255 home care workers would be recruited for baseline measures if the invitation is distributed to all 440. Assuming a 20% attrition rate, 204 home care workers will complete both baseline and post-intervention measurements, which would result in 102 participants in both the control and intervention arms.

We do not expect different effects in the clusters of intervention and control units since the clusters are made based on feasibility and convenience. With 102 participants in each arm, and an alpha of 5%, we have an 80% chance of detecting an effect size (i.e. an intervention effect) corresponding to a Cohen’s d of 0.39. As no data on the variance in pain scores following a working day in the home care sector currently exist, we were guided by the variance (10.6) from a Goldilocks Work intervention in an industry setting [25], based on which a Cohen’s d of 0.39 would correspond to an intervention effect of 1.27 points. Given that a 1.74 difference on the numeric rating scale between control and intervention is recognized as clinically significant [26, 27] we find that a sample comprising 204 participants is sufficient to detect a clinically meaningful difference.

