### Statistical methods

To evaluate the primary outcomes, lower back pain and shoulder/neck pain in the intervention and the control group will be compared after the 16-week intervention, applying the intention-to-treat principle [34]. When conducting analyses, special considerations will have to be taken due to the clustered trial design [35, 36]. We will therefore adjust analyses for the effects of clustering by using mixed-model methods to account for differences between clusters while still providing insight into changes at the individual level [37]. Mixed-models will also be used to account for repeated measurements of pain intensity and fatigue at the individual level both at baseline and post-intervention. Parametric or non-parametric tests will be applied as appropriate.

Further, for physical behavior measures, compositional data analysis (CoDA) will be utilized as appropriate for time-use data [38, 39].

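### The stated 80% power for d = 0.39 (1.27 points) is that of an individually randomised comparison; with 11 randomised units it is lower, and the claim that 204 participants suffice for 1.74 points depends on an unstated within-unit correlation

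*Protocol article*

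**What the plan says.** The Sample size section expects 440 eligible workers, 58% participation (255 recruited) and 20% attrition, leaving 204 completers or 102 per arm. On clustering it says only this: "We do not expect different effects in the clusters of intervention and control units since the clusters are made based on feasibility and convenience". It continues: "With 102 participants in each arm, and an alpha of 5%, we have an 80% chance of detecting an effect size" corresponding to d = 0.39. For the scale, "we were guided by the variance (10.6) from a Goldilocks Work intervention in an industry setting", so that d = 0.39 "would correspond to an intervention effect of 1.27 points". It then reasons: "Given that a 1.74 difference on the numeric rating scale between control and intervention is recognized as clinically significant", "we find that a sample comprising 204 participants is sufficient to detect a clinically meaningful difference". It gives no intra-cluster correlation (ICC) or design effect, and the number of units does not enter the calculation.

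Elsewhere, the Abstract and the Randomization section allocate about 11 whole units 1:1. The Statistical methods section commits to a clustered analysis: "We will therefore adjust analyses for the effects of clustering by using mixed-model methods to account for differences between clusters".

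**The concern.** The power is stated for a design in which 204 workers are randomised and respond independently. This trial randomises units.

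The reason given for setting clustering aside answers a different question. Whether the intervention works equally well in every unit is effect heterogeneity. The loss of precision in a cluster trial comes from workers in the same unit having more similar pain scores than workers in different units, and that remains even if the effect is identical everywhere. How the units came to be formed does not make their workers independent.

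The protocol itself gives grounds to expect some correlation. The Randomization section chooses units because their workers communicate and cooperate, and Program design and production notes that average physical demand differed between units.

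At stake is how a null result is read. If readers believe the trial had 80% power for 1.27 points and ample power for 1.74, they may take a non-significant result as evidence against a relevant effect when the design could not support that.

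**Working it through.** **Inputs from the protocol.** 102 completers per arm, alpha 5% (two-sided reproduces the figure), d = 0.39, variance 10.6, clinically significant difference 1.74 points, 11 units.

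**Assumed inputs.** ICC from 0.01 to 0.10; equal unit sizes, with a coefficient of variation (CV) of 0.4 as a sensitivity; 11 − 2 = 9 degrees of freedom for the unit-level comparison, with the normal approximation alongside.

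**Step 1: the plan's own figure.**
- 440 × 0.58 = 255; 255 × 0.8 = 204; 204/2 = 102.
- SD = √10.6 = 3.256; 0.39 × 3.256 = 1.27 points.
- Power of a two-sample test at d = 0.39 with 102 independent people per arm: 79.2% (t, 202 df) or 79.5% (normal).

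The stated 80%, 0.39 and 1.27 are all recovered with a design effect of exactly 1.

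**Step 2: allow for units.**
- Mean completers per unit m = 204/11 = 18.5.
- Design effect DE = 1 + (m − 1) × ICC = 1 + 17.5 × ICC.
- SE = √(10.6 × DE × 2/102) = 0.456 × √DE.
- Detectable difference at 80% power = 2.80 × SE (normal) or 3.15 × SE (noncentral t, 9 df).

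| Assumed ICC | DE | Power for 1.27: t, 9 df / normal | Detectable difference: t, 9 df / normal | Power for 1.74: t, 9 df / normal |
|---|---|---|---|---|
| 0.01 | 1.18 | 63% / 73% | 1.56 / 1.38 | 88% / 94% |
| 0.02 | 1.35 | 57% / 67% | 1.67 / 1.48 | 83% / 91% |
| 0.05 | 1.88 | 44% / 53% | 1.97 / 1.75 | 70% / 79.5% |
| 0.10 | 2.75 | 32% / 39% | 2.38 / 2.12 | 54% / 63% |

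At ICC 0, a test on 9 df has about 70% power for 1.27 points. Splitting the units 5 and 6 instead of using equal arms shifts the t-based detectable differences by about 0.01 point and power by no more than about one percentage point.

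**Step 3: where the 1.74-point claim stops holding, without baseline adjustment.**
- t, 9 df: DE may reach (1.74/3.15)² / 0.2078 = 1.468, where 0.2078 = 10.6 × 2/102. ICC = 0.468/17.5 = 0.027.
- Normal: DE may reach (1.74/2.80)² / 0.2078 = 1.856. ICC = 0.856/17.5 = 0.049.
- With CV 0.4, DE = 1 + ((1 + 0.16) × 18.5 − 1) × ICC = 1 + 20.5 × ICC. The limits become 0.023 and 0.042.

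**Step 4: what baseline adjustment could return.** Take an adjusted variance of 10.6 × (1 − r²), with r the assumed baseline-post correlation and the ICC held fixed.
- r = 0.5, ICC 0.05, 9 df: 1.97 × √0.75 = 1.70 points, inside 1.74.
- r = 0.6, ICC 0.01, 9 df: 1.56 × 0.8 = 1.25 points, close to the stated 1.27.

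**The case against.** The strongest reply is that the calculation above leaves out features of the stated design. The primary outcomes are changes from baseline, rated after each working day for a week at both times, and the mixed model will use those repeated ratings. The protocol does not say whether 10.6 is the variance of single ratings, weekly means or changes. Clustering raises the effective variance, while baseline and repeated ratings may lower it, so the net direction is open. This stands, and is why the result on 1.74 points must be conditional. It does not rescue the stated 80%, because the Sample size section takes no credit for either feature and its figure is exactly the unclustered calculation.

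It is also fair that 9 df and CV 0.4 are the review's inputs. The protocol names no degrees-of-freedom method, which commonly belongs to the SAP, and the range of 23 to 95 workers per unit counts employees, not completers. With the normal approximation and equal sizes, power for 1.27 points is still below 80% at every positive ICC.

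Three stronger readings are tempting, and the documents do not support them:
- **That 204 participants cannot detect 1.74 points.** Even without baseline credit, power is 88% at ICC 0.01 and 83% at ICC 0.02 on 9 df. The documents give no ICC that would settle the matter.
- **That the planned analysis ignores clustering.** Statistical methods commits to adjusting for it, so the defect lies in the power statement and not in the analysis.
- **That the protocol's sums are wrong.** They are right for the design they describe; that design is not this one.

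**Conclusion.** The point holds in this form. The 80% power for 1.27 points is not a property of an 11-unit cluster trial, and the sentence standing in for a clustering allowance does not address within-unit correlation. On the protocol's variance, with equal unit sizes and no baseline adjustment, an assumed ICC between 0.01 and 0.10 gives power of 63% down to 32% on 9 df (73% down to 39% by normal approximation).

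The sufficiency claim for 1.74 points is neither established nor refuted. It depends on an ICC and a baseline-post correlation that the protocol does not state, and it is written as unconditional.

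**What to change.** In the Sample size section:
1. Delete the sentence about not expecting different effects in the clusters.
2. Restate power and detectable difference with a design effect and small-cluster degrees of freedom, over a stated range of ICC and baseline-post correlation. Say what the variance of 10.6 refers to.
3. Make the statement that 204 participants suffice conditional on those ranges.

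The Randomization section conceals allocation until baseline is complete, so the baseline ratings may be used before allocation is revealed to update the variance and the ICC. An ICC from 11 units will be imprecise and should be shown with its uncertainty. Baseline data alone cannot give the baseline-post correlation, which must stay an assumed range.

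The cost is one rewritten paragraph, a registry note of the kind that Data Availability already promises for important protocol changes, and a less favourable stated figure. No extra participants are needed.

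### Two unranked primary pain outcomes, but the trial is sized as one test at an undivided 5% alpha, with no statement of whether either or both must succeed

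*Protocol article*

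**What the plan says.** The abstract states: "Musculoskeletal pain in neck/shoulder and lower back will be the primary outcomes". The Primary outcomes section lists the change in lower back pain and the change in shoulder/neck pain as separate items, in no order of priority, and continues: "Both primary outcomes will be measured after each working day during 1 week at baseline and 1 week at the end of the intervention".

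The Sample size section contains one calculation, for an outcome it does not name: "With 102 participants in each arm, and an alpha of 5%, we have an 80% chance of detecting an effect size", "corresponding to a Cohen’s d of 0.39". The conversion to points rests on one outside figure: "we were guided by the variance (10.6) from a Goldilocks Work intervention in an industry setting". This gives 1.27 points, which the section compares with a clinically significant difference of 1.74.

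The Statistical methods section says that both sites will be compared between arms with mixed models. The article gives no ranking, alpha split or rule for combining the two results.

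**The concern.** With two primary outcomes, alpha and power for the trial depend on how the two results combine into a conclusion. A 5%/80% pair for one unnamed outcome does not describe that conclusion until the rule is known.

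The rule matters here. The abstract and the Strengths and weaknesses section both speak of possible national use if the intervention is proven effective, but the article does not define what would prove it. The trial is also unblinded with self-reported pain. An open rule would let the claim rest on whichever site happens to reach significance.

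**Working it through.** **Inputs from the article.** 102 per arm; alpha 5%; d = 0.39; variance 10.6, so SD = √10.6 = 3.256; two primary outcomes. Sidedness and the correlation between the two test statistics are not given. I take the correlation as an assumption and show a range.

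**1. Reproduce the stated power.** The noncentrality is 0.39 × √(102/2) = 2.785.
- Two-sided 5%: Φ(2.785 − 1.960) = 79.5% (79.2% with the noncentral t).
- One-sided 5%: 87.3%.
- Effect in points: 0.39 × 3.256 = 1.27, as stated.

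The article's 80% is therefore the power of one two-sided test at the full 5%.

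**2. If either site suffices, each tested at two-sided 5%.** The family-wise error is 1 − P(|Z₁| < 1.96, |Z₂| < 1.96), with (Z₁, Z₂) bivariate normal. A false finding of benefit uses only the favourable 2.5% tail of each test.

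| Assumed correlation | Any false difference | False benefit |
|---|---|---|
| 0 | 9.75% (= 1 − 0.95²) | 4.9% (= 1 − 0.975²) |
| 0.3 | 9.5% | 4.8% |
| 0.5 | 9.1% | 4.5% |
| 0.7 | 8.3% | 4.2% |
| 0.9 | 7.0% | 3.5% |

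The first column of results compares with a nominal 5%, the second with a nominal 2.5%.

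**3. If both sites must be significant, each at 5%.** Alpha needs no split. The error is at most 5% when only one null is true, and far lower when both are. Joint power with d = 0.39 at both sites is 0.795² = 63% at correlation 0, 66% at 0.3, 68% at 0.5 and 71% at 0.7.

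**4. If alpha is shared (Bonferroni, or the first Holm step, at two-sided 2.5%).**
- Power for a given site at d = 0.39: Φ(2.785 − 2.241) = 70.7% (70.1% with the noncentral t).
- Detectable d at 80% power: (2.241 + 0.842) × √(2/102) = 0.432 (0.434 with the noncentral t), or about 1.41 points at SD 3.256.
- Keeping 80% power at d = 0.39 in the first step would take 125 per arm.

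The 70% is a floor for a site under Holm. If both sites truly have d = 0.39 and the tests are independent, the second step raises it to 0.707 + (0.795 − 0.707) × 0.707 = 76.9%.

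Steps 2 to 4 use the article's own calculation, which makes no allowance for clustering, and assume tests that hold their nominal level.

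**The case against.** The strongest objection is that multiplicity procedures and success rules usually sit in a statistical analysis plan. None is shown here, and a condensed article is not at fault for leaving them there. That stands as far as the procedure itself goes. It does not cover the sample-size statement, which the article does fix: the 80% belongs to one unadjusted test, while two outcomes are primary and unranked. Whatever an analysis plan says, that section needs a sentence to show what its figures refer to.

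A reader might infer that a significant result on either site is planned to count as proof, so that the chance of falsely claiming the intervention works is 9% to 10%. The documents do not support this, for three reasons:

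- **The either-site rule is not written.** Nor does the article say in so many words that each outcome is tested at 5%. The stated objective names both sites, so a both-required rule is equally open.
- **The figure counts differences in both directions.** The stated power reproduces only with two-sided tests, and for those a false claim of benefit is about half as large.
- **A value of 9% or more needs a correlation of about 0.5 or less.** None is given, and two pain scores from the same worker on the same scale are probably positively correlated.

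Two further points also stand. The detectable effect at 2.5% remains below 1.74 points, so the article's conclusion that its sample is sufficient does not fall on this ground. And Holm is one option among several: a stated hierarchy, for example, would keep the full 5% for the first-ranked site.

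**Conclusion.** The point holds in a limited form. The article fixes two unranked primary outcomes and sizes the trial as one two-sided 5% test without saying how the two results combine.

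- **Either site suffices, at 5% each:** power per site stays near 80%, but the chance of at least one false significant difference is about 7% to 9.75%. A false finding of benefit is about 3.5% to 4.9%, against a nominal 2.5%.
- **Both required:** the error is controlled, but joint power is about 63% to 71%.
- **Alpha shared:** the error is controlled, but power in the first step is about 70%.

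The error range assumes a correlation of 0.9 to 0 and the joint-power range a correlation of 0 to 0.7. All figures take the article's variance and unclustered calculation as given. With about 11 units, the actual error rate also depends on how clustering is handled, which is a separate matter.

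**What to change.** State in the Statistical methods section that the two primary outcomes are tested with the Holm procedure at a family-wise two-sided 5%: the smaller p-value against 2.5% and, if it passes, the other against 5%. Add that an effect is claimed only for a site that passes.

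Restate the Sample size section for the first step at 2.5%: with 102 per arm, the detectable d is about 0.43 (1.41 points at variance 10.6), and power at d = 0.39 is about 70%, before any allowance for clustering. If the investigators intend that both sites must succeed, they should say so and report joint power in place of the 80%.

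The cost is a few sentences and a somewhat less favourable power figure. No participants or measurements are added.
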